### Measurement of exposures and confounding variables

Exposures and confounding factors will be measured using parent-completed questionnaires, specific to the age of the child (0–12 months, 13–36 months and 37–59 months). The development, piloting and validation of the questionnaires are described in the protocol for the falls case–control study.^38^

### Analysis

The analysis of the validation of exposures has been described in the falls case–control study protocol.^38^ Relationships between exposures, potential confounding variables and scalds will be explored using causal diagrams. These will be used to identify the minimal set of potential confounding factors to adjust for when estimating ORs. Exposure and confounding variables will be described using frequencies and percentages for categorical variables and means (and SDs) or medians (and IQRs) for continuous variables as appropriate.

Conditional logistic regression will be used for the analysis of cases and matched controls to estimate ORs and 95% CIs, unadjusted and adjusted for confounding variables. All models will a priori adjust for deprivation and distance from hospital. Unconditional logistic regression will be used for the analysis of cases and hospital controls. All models will a priori be adjusted for age, gender, deprivation and distance from hospital, in addition to other potential confounding variables, as described for the matched analysis. Effect modification will be investigated by adding interaction terms to models and where present (p<0.01), stratified results will be reported. Results will also be stratified by the type of service used (child treated in ED or admitted to hospital vs no treatment required) as a proxy for injury severity.

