## Introduction

Burn injuries in children under 10 years of age are a major cause of death internationally, and are the fifth most common cause of non-fatal childhood injuries.^1^ In those under 5 years, scalds are the leading cause of thermal injuries in high, middle and low income countries.^2–14^ Scalds accounted for 62% of hospital admissions for thermal injuries in children under 5 years old in the USA between 2003 and 2012,^15^ and 63% of such admissions in the same age group in England in 2012–2013.^16^ In 2012–2013 over 3500 children aged 0–14 years were admitted to hospital in England with a thermal injury, of which the majority (61%) were scalds.^16^ Most scalds in childhood occur at home^12^
^13^
^17^ and are most commonly caused by hot liquids from kettles, baths, cups or mugs.^17^^–^19

Paediatric scald injuries impose a heavy financial burden on the state. More severe scalds may require intensive care, skin grafts and months or years of rehabilitation.^2^ Studies from England suggest the average cost of treating an uncomplicated minor (<10% total body surface area) paediatric scald in 2002–2003 was £1850^20^ while the average cost of acute inpatient treatment of a ‘major scald’ (30–40% total body surface area) in 2007–2009 in a paediatric burns unit can be as high as £55 000.^21^ Socioeconomic disadvantage increases the risk of scalds. Recent research from the UK demonstrates that children living in the most disadvantaged areas have an 82% higher odds of a medically attended scald injury than those in the most affluent areas.^22^ This pattern is repeated globally, with socioeconomic differentials between and within countries.^12^
^13^
^23^

Systematic reviews and recent meta-analyses have consistently demonstrated that interventions to promote thermal safety in the home can increase safety behaviour and the use of safety equipment to reduce the risk of thermal injuries.^24–31^ However, there remains little evidence that they reduce the actual incidence of thermal injuries due to a lack of adequately powered randomised controlled trials or high quality observational studies. Rigorous case–control studies have often provided the best evidence for effective interventions in injury prevention.^32–34^ There are few case–control studies investigating prevention practices in the homes of scalded children.^23^

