^35–37^ One Canadian multicentre study, exploring risk and protective factors for a range of childhood injuries requiring emergency department (ED) attendance in children under the age of 8 years, failed to find any significant associations between any scald prevention practices and ED attendance.^35^ A second study of children of all ages attending EDs in two hospitals in Greece with a thermal injury found a 40% reduction in the odds of injury with a one unit increase in a burn avoidance index which measured four scald prevention behaviours.^36^ Another study, of children aged 0–5 years attending an Iraqi hospital with an acute burn injury found a one unit increase in the number of thermal hazards increased the odds of a thermal injury by 32%.^23^ Finally a study of children aged 0–4 years attending EDs in 14 Dutch hospitals found that using a vacuum flask rather than cups or mugs, to store hot drinks halved the odds of ED attendance for a thermal injury.^37^ These studies were limited by small sample sizes,^36^
^37^ the use of hospital controls,^23^
^35^
^36^ the use of unvalidated parental reports to measure exposures,^23^
^36^
^37^ case definitions covering a wide range of injury mechanisms^35^ and potential bias from unmeasured confounders.^23^
^35–37^

The aim of the case–control study described in this protocol is to examine the relationship between modifiable risk factors and scald injuries in young children. Community and hospital controls will be used and a range of confounding factors will be measured and adjusted for. Parental reported exposures will be validated by home observations in a sample of cases and controls.

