### Definition of cases and controls

Cases will be defined as children under the age of 5 years who received medical attention for a scald injury which occurred in their home or garden, defined as the address at which they were registered with a family doctor or general practitioner (GP). Scald injuries are defined as ‘thermal injuries caused by hot liquids or steam’. Medical attention is defined as an admission to hospital or attendance at an ED or MIU. Children are not eligible to take part if the injury was intentional or suspected to be intentional or if the child lives in residential care. Fatal injuries will not be included to avoid parental distress. Cases are not eligible to be included as a control in the study at any time after being recruited as a case.

Controls are defined as children under the age of 5 years who did not receive medical attention for a scald injury on the date of the case's medical attendance. Children living in residential care are not eligible to participate in the study. Controls are eligible for recruitment to the study as a case or as a further control if they are recruited at least 12 months after their first recruitment. Controls will not be recruited more than twice to the study.

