### Definition of exposures and confounding variables

Exposures relating to scalds will be categorised into safety (and other potentially risk reducing) equipment use, safety behaviours and home hazards (see table 1). Cases will be asked about exposures relating to the 24 h (or 1 week for less frequent behaviours) before the scald injury. Controls will be asked about exposures for the 24 h (or 1 week for less frequent behaviours) prior to completing the questionnaire. A range of potential confounding factors will be measured as shown in table 1.

**Table 1 INJURYPREV2014041255TB1:** Definition of exposures and confounding variables

*Exposure: Safety and other potentially risk reducing equipment use* Use of safety gates Kettles with curly or short cables Play pens (or travel cots) Stationary activity centres *Exposure: Safety behaviours* Not drinking hot drinks while holding a child Not passing hot drinks over a child Keeping hot drinks out of reach of children Storing kettles at back of work tops Use of back rings on cooker Turning saucepan handles away from edge of cooker Not using tablecloths Knowledge of hot tap water/thermostat temperature Using cold water first when running a bath Measuring bath water temperature Not leaving child without an adult in the bath or bathroom Not having children running baths Teaching children safety rules about hot liquids *Exposure: Home hazards* Has baby walker	*Potential confounders: sociodemographic* Age Gender Ethnic group Family size and structure Housing tenure Receipt of state-provided means-tested benefits Single parenthood Adult unemployment in the household Overcrowding Deprivation (measured using the Index of Multiple Deprivation^39^) Distance of residence from hospital Use of out-of-home childcare *Potential Confounders**:** child and parent measures for health and behaviour* Child behaviour (infant, early child and child behaviour questionnaires)^40–42^ Child health status (VAS^43^; PedsQL^44^ ^45^) Long-term health conditions Parental mental health (Hospital Anxiety and Depression Scale)^46^ Parenting daily hassles^47^ ^48^ Parental perception of child's ability to reach hot liquids (a series of questions on climbing, reaching, turning on taps, ability to open safety gates)

PedsQL, pediatric quality of life inventory; VAS, visual analogue scale.

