### Sample size

Based on data on the prevalence of exposures and the amount of missing data obtained from analysis of the first 428 controls recruited across all the ongoing case–control studies, 259 cases and 1036 matched controls are required to detect an OR of 0.64 (equivalent to an OR of 1.56 for a risk factor), with 80% power, a 5% significance level, a correlation between matched cases and controls of 0.1 and an average of four controls per case.

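### About 12 of the 18 listed exposures can plausibly affect only one scald source, but the only outcome described is all scalds pooled, so their odds ratios are diluted towards 1 and a near-null result could be misread

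*Protocol article*

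**What the plan says.** Under Definition of cases and controls, cases are "children under the age of 5 years who received medical attention for a scald injury which occurred in their home or garden", with a scald meaning any thermal injury from hot liquid or steam. The Objectives section likewise refers to medically attended scalds as a whole. The Introduction says that childhood scalds "are most commonly caused by hot liquids from kettles, baths, cups or mugs", so the outcome combines several sources.

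Table 1 lists 18 exposures, many tied to one of those sources, for example "Using cold water first when running a bath Measuring bath water temperature Not leaving child without an adult in the bath or bathroom".

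The Analysis section uses causal diagrams to choose confounders ("Relationships between exposures, potential confounding variables and scalds will be explored using causal diagrams"). It then compares cases with matched controls by conditional logistic regression, and with hospital controls by unconditional logistic regression. Two subdivisions are named: interaction terms, with stratified results where p<0.01, and strata by type of service as a proxy for severity. Scald source is not mentioned.

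The Sample size section gives one target for all exposures: "259 cases and 1036 matched controls are required to detect an OR of 0.64 (equivalent to an OR of 1.56 for a risk factor". The other inputs it states are four controls for each case on average, a case-control correlation of 0.1, a 5% level and 80% power.

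**The concern.** A practice that acts on one source cannot be expected to prevent scalds from another. Running cold water first has no evident route to preventing a scald from a mug. Cases from unrelated sources therefore contribute an OR near 1 and pull the pooled estimate towards 1.

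The planned interaction terms cannot recover the source-specific effect. Source is defined only for cases, and a control has no scald source to interact with.

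The Discussion says that the findings should inform prevention policy and home-safety advice. For a bath, kettle or cooker practice, a pooled OR close to 1 could be read as evidence that the practice does not work, when it may only show that the practice concerns a minority of scalds.

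**Working it through.** **Exposure count (Table 1).** Bath or tap water 5, hot drinks 3, kettle 2, cooker 2: 5 + 3 + 2 + 2 = 12. The other 6 are safety gates, play pens, activity centres, tablecloths, teaching rules and baby walker. Tablecloths are arguable and could be counted as a thirteenth.

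**The plan's own figure.** 259 × 4 = 1036, and 1/0.64 = 1.5625, in line with the printed 1.56. The 259 cannot be confirmed, because the exposure prevalence and the missing-data fraction are not printed. Dupont's formula for matched case-control studies (4 controls per case, correlation 0.1, two-sided 5% assumed, 80% power, OR 0.64) returns 259 at a control prevalence of about 33% or 77% without inflation for missing data. Its minimum is about 207, near 56%. Since 207/259 = 0.80, the figure also fits about 20% missing data. It is plausible.

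**Dilution.** Let f be the relevant source's share among unexposed cases, and let other sources have OR 1. With a rare outcome:

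pooled OR = 1 − f(1 − OR_source)

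The relevant share among all cases is smaller if the practice is protective. With control prevalence p it is f(1 − p + p·OR_source) / (1 − p + p·OR_pooled).

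Example with p = 0.5, f = 0.5, OR_source = 0.64:
- pooled OR = 1 − 0.5 × 0.36 = 0.82
- relevant share = 0.5 × (0.5 + 0.32) / (0.5 + 0.41) = 0.41/0.91 = 0.45
- relevant cases = 0.45 × 259, about 117

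**Power.** Dupont's formula, with 259 sets for the pooled analysis and only the relevant sets for the restricted one. OR_source is assumed to be 0.64. Power ranges cover prevalences from 33% to 77%; case counts are at 50%.

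| f (assumed) | Pooled OR | Pooled power | Relevant cases | Restricted power |
|---|---|---|---|---|
| 0.15 | 0.95 | 6–7% | 33 | 16–19% |
| 0.3 | 0.89 | 11–13% | 67 | 29–35% |
| 0.5 | 0.82 | 24–28% | 117 | 46–55% |
| 0.7 | 0.75 | 44–53% | 170 | 61–71% |

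Restriction has more power in every row, despite fewer cases.

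**Stronger effects.** At OR_source 0.50 and f = 0.5, using the two prevalences that return 259, pooled power is 43–44% and restricted power 79–81%. At OR_source 0.36, pooled power is 68–77% at f = 0.5 and above 95% at f = 0.7, over prevalences of 33% to 77%.

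**What the design OR implies.** For the pooled OR to equal 0.64, OR_source must be 1 − 0.36/f:
- f = 0.6: 0.40
- f = 0.5: 0.28
- f = 0.4: 0.10
- f = 0.36: 0

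Below f = 0.36, even a practice that prevented every scald of its type would not give a pooled OR of 0.64.

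**Two separate losses.** At 50% prevalence, 259 sets give 88% power at OR 0.64. At f = 0.5 this falls to 55% because fewer cases are relevant, and then to 28% through pooling. At f = 0.3 the sequence is 88%, 35%, 13%. Restriction recovers only the second step.

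**The case against.** The strongest reply is that the pooled OR is the right answer to the stated objective. The effect of a practice on all medically attended scalds is a legitimate prevention quantity. This stands: the pooled OR is a diluted estimand, and a reader who inferred that it is biased or invalid would go too far.

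A reader might also infer that pooling loses most of the power, or that effective practices will look ineffective. The documents do not support either as a general statement. They give no source shares and no source-specific ORs, and 0.64 is stated as the detectable OR for the case-control comparison, not for one source. Much of the shortfall at small shares is scarcity of relevant cases, which no re-analysis cures. The Introduction itself reports a study in which a hot-drink practice halved the odds of attendance for any thermal injury, so a single-source practice can show a strong pooled effect.

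It is also tempting to say that the plan repeats a fault it criticises in others, "case definitions covering a wide range of injury mechanisms". That remark concerns a study of many kinds of childhood injury. Restricting cases to scalds already narrows that problem; what remains is a milder form of it.

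Finally, this is a condensed article that refers to a companion falls protocol for more detail on methods, and a source-specific analysis could sit in a fuller plan. That limits how strongly the point can be put. It does not remove it, because the article states its outcome and names its subdivisions, and a protocol on falls is unlikely to define scald sources. The causal-diagram sentence does not itself fix the pooling; the case definition and the stratification sentence do.

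**Conclusion.** The point holds as a cheap improvement, not as an error in the planned estimate. Followed as written, the analysis gives diluted ORs for about 12 of 18 exposures, and no subdivision that the article names would show the source-specific effect. At a source-specific OR of 0.64, restricting to the relevant matched sets roughly doubles to triples the power for shares of 0.15 to 0.5, and still helps at 0.7.

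The size rests on assumptions: the shares, the source-specific ORs, an OR of 1 for unrelated sources, a rare outcome, a two-sided test, and prevalences of 33% to 77%. The direction of the dilution needs only that unrelated sources have an OR near 1. The loss is small where one source dominates and the effect is strong, but at most one source can supply more than half of the cases, so that cannot describe all four groups of exposures.

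**What to change.** In the Analysis section:

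- Before analysis, map each source-specific exposure in Table 1 to the scald source or sources that it can affect: bath or tap water, hot drinks, kettle, or cooker. Decide where tablecloths belong.
- For those exposures, report the OR from matched sets whose case had the relevant source, beside the all-scald OR. Apply the same restriction to cases in the hospital-control analysis.
- Keep all scalds as the outcome for general exposures such as safety gates, play pens, activity centres, baby walkers and teaching rules.
- State that the all-scald OR of a source-specific exposure is its effect on total scalds, and that a value near 1 is not evidence that the practice does not work.

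The cost is analysis-plan wording and coding the source of each case's scald, assuming the circumstances of the injury are recorded. No extra participants are needed. The drawback is fewer cases and wider confidence intervals: at OR 0.64 the source-specific estimates stay below 80% power at every share examined, and the report should say so. Fixing the map in advance also guards against choosing subgroups after seeing the data.

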### Recruitment of cases and controls

Participants will be recruited during or after their hospital admission or attendance at the ED or MIU. The initial approach to potential participants will be made by clinical staff, followed by contact from researchers where agreement for this is given. Researchers will contact potential participants during their medical attendance, or by telephone or postal invitation within 72 h of ED or MIU attendance. Postal and telephone reminders will be used if no response is received within 2 weeks. Participants will be given a £5 voucher for local stores to thank them for participation in the study.

Controls will be recruited from the community (matched community controls) and from the hospital (unmatched hospital controls). Community controls will be identified from the GP practice where the case is registered, and matched with the case on age (within 4 months) and gender. If the GP practice where the case is registered does not consent to take part, the GP practice closest to the case's GP practice will be asked to recruit controls. GPs or Primary Care Trust staff will invite, by post, parents or guardians (hereafter referred to as parents) of 10 children for each recruited case to take part in the study. One reminder will be sent to non-responders (controls and cases) if they have not replied within 2 weeks of initial mailout. Hospital controls will comprise children already recruited as a case to one of the other ongoing case–control studies, that is, these will be children aged 0–4 years attending the ED or MIU with another injury mechanism (fall on the same level, fall from furniture, staircase fall or poisoning).

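### The matched models do not fix age as a covariate, although controls report a later exposure window than the one matching aligns

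*Protocol article*

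**What the plan says.** The Analysis section of the protocol article sets two fixed adjustment lists. For cases and matched community controls: "All models will a priori adjust for deprivation and distance from hospital". For the unmatched hospital-control comparison the list is longer: "All models will a priori be adjusted for age, gender, deprivation and distance from hospital, in addition to other potential confounding variables". Further covariates come from causal diagrams: "These will be used to identify the minimal set of potential confounding factors to adjust for when estimating ORs". Table 1 names age among the potential confounders, so age can enter the matched models by that route but is not guaranteed to.

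Under Recruitment of cases and controls, community controls are "matched with the case on age (within 4 months) and gender". Ten children per recruited case are invited by post, with one reminder after 2 weeks without a reply. The article does not give the date at which the two ages are compared.

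Under Definition of exposures and confounding variables, the reporting windows have equal length but different anchors. For cases: "Cases will be asked about exposures relating to the 24 h (or 1 week for less frequent behaviours) before the scald injury". For controls: "Controls will be asked about exposures for the 24 h (or 1 week for less frequent behaviours) prior to completing the questionnaire".

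**The concern.** Leaving age out of the fixed list for the matched models makes sense if matching has already dealt with it. Matching aligns age at selection, but the exposure is measured later in controls. The control is chosen after the case has been recruited, receives a letter, may need a reminder, and then reports on the day or week just before completing the form. The case reports on the day or week before an injury that has already happened.

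For an exposure that changes quickly as a child starts to crawl and walk, a systematic age difference at exposure is a confounder. Controls who are older at exposure will have more of anything that rises with age, so that item will look protective. Items that fall with age will be biased the other way. This would affect the matched comparison, which is the one the sample size is built on.

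**Working it through.** **Plan's own figure.** The article gives no lag and no rate of change with age, so there is nothing to reproduce on this point. The sample size figures (259 × 4 = 1036; 1/0.64 = 1.5625) are consistent and do not bear on it.

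**Does a lag follow from the design?** Children are selected before they are invited, so their completion dates are unknown at selection.
- If matching is on date of birth, or on age at any common date, the whole interval from injury to completion remains.
- If the control's age at mailing is matched to the case's age at injury, only the response time remains.

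Either way controls are, on average, older at exposure than when matched. The direction follows from the text; the length does not.

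**Inputs.**
- From the article: caliper of 4 months either way.
- Assumed: true OR of 1; exposure prevalence p in cases of 0.3 to 0.7; exposure odds multiplied by g per month of age; lag L in months; control age at matching uniform within the caliper.

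**Formula.** Control prevalence = average over U ~ Uniform(−4, 4) of expit[logit(p) + ln(g) × (L + U)]. Apparent OR = odds(p) / odds(control prevalence). Without U this reduces to g^(−L). For example, with g = 1.10 and L = 2, 1/1.21 = 0.826; the full formula at p = 0.5 gives 0.828.

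**Apparent OR when the true OR is 1** (range over p = 0.3 to 0.7):

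| Odds factor per month | L = 0 | L = 0.5 | L = 1 | L = 2 |
|---|---|---|---|---|
| 1.02 | 1.000 | 0.990–0.991 | 0.980–0.981 | 0.961–0.962 |
| 1.05 | 0.997–1.003 | 0.973–0.978 | 0.950–0.955 | 0.905–0.910 |
| 1.10 | 0.990–1.010 | 0.945–0.963 | 0.901–0.919 | 0.820–0.836 |
| 1.20 | 0.967–1.034 | 0.885–0.947 | 0.811–0.868 | 0.681–0.727 |

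The L = 0 column is the caliper acting alone. The bias is in the other columns.

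**Does adjustment remove it?** Conditional logistic regression was simulated with 12,000 sets, 1:4 matching, p = 0.5 and true OR 1:

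| Odds factor per month | Lag (months) | OR without age | OR with age at exposure |
|---|---|---|---|
| 1.05 | 1 | 0.974 | 1.022 |
| 1.05 | 2 | 0.918 | 1.025 |
| 1.10 | 0 | 1.022 | 1.021 |
| 1.10 | 2 | 0.842 | 1.025 |
| 1.20 | 1 | 0.820 | 0.975 |
| 1.20 | 2 | 0.702 | 1.008 |

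Simulation error: the standard error of the log OR is about √[(1 + 1/4)/(12,000 × 0.25)] = 0.020. The adjusted values lie within about 1.3 standard errors of 1.

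**Scale against the study's own precision.** With 259 sets, p = 0.5 and the within-set correlation ignored, the standard error of the log OR is about √[1.25/(259 × 0.25)] = 0.139. Apparent ORs (p = 0.5) of 0.953 (g = 1.05, L = 1), 0.828 (g = 1.10, L = 2) and 0.705 (g = 1.20, L = 2) are log biases of 0.048, 0.189 and 0.350, or about 0.35, 1.4 and 2.5 standard errors. This supposes that every set lies in the age range of rapid change; sets outside it dilute the bias.

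**The case against.** The strongest reply is that the quoted sentence is a minimum, not the full model. Table 1 lists age, and also parents' perception of whether the child can reach hot liquids, a developmental measure close to the suspected mechanism. Either may be selected by the causal diagrams. This stands against any claim that the matched models ignore age. It does not remove the point: both are only candidates, whereas the same section does not leave age to the diagrams in the hospital-control models.

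A second reply is that the size is conjecture. The only intervals in the recruitment section are 72 hours for researcher contact and 2 weeks before a reminder; a lag of 1 to 2 months is assumed, and so is the monthly change. Kettle cables, tablecloths, cooker rings and saucepan handles have no evident month-by-month dependence on a child's age. All of this stands and limits the reach of the point.

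Three stronger readings are tempting, and the documents do not support them:
- *A 4-month caliper is itself too wide.* If controls fall evenly either side of the case's age, the apparent OR stays within 0.97 to 1.03 even at a factor of 1.20 per month.
- *The bias could by itself produce the effect the study is powered to detect.* Values near that size need the longest lag and the steepest slope considered, both assumed, across the whole sample. Such a slope can hold only over a short age band, while the study covers children up to 5 years.
- *Sets that straddle the questionnaire age bands compare different exposure items.* The article says the forms are age-specific, but not that their exposure questions differ, and it refers to the falls study protocol for questionnaire development.

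The article also refers to the falls protocol for methods in general. The missing reference date for matching is therefore a matter to clarify, not a demonstrated gap.

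**Conclusion.** The point holds in a limited form. Age is not fixed in the matched models, and the two exposure windows are anchored so that controls tend to be older at exposure than when matched. The omission and the direction of the lag rest on the text; the size does not. For a lag of 1 to 2 months and exposure odds rising by a factor of 1.05 to 1.20 per month, a true OR of 1 appears as about 0.96 to 0.68. With a factor of 1.02, even a 2-month lag gives 0.96. The lower end is small beside the study's sampling error; the upper end is not. The concern is confined to exposures that change quickly with age. It justifies a nearly free improvement to the plan and does not put the whole matched analysis in doubt.

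**What to change.** Amend the sentence on the conditional models in the Analysis section so that the fixed list also includes age at each child's own exposure window: age at injury for cases and at questionnaire completion for controls. Enter it as a flexible term, such as linear plus quadratic or a small spline. State the reference date at which ages are compared for matching.

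The age coefficient should be treated as a nuisance term, because the design itself creates part of the age difference between case and control. The adjustment works because the spread within the caliper lets case and control ages overlap despite the lag.

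The statistical cost is one to three degrees of freedom. The change presumes that date of birth, injury date and completion date are available, which the article does not state. Recruitment and the choice of children to invite stay as they are.

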### Study design

A multicentre case–control study will be carried out within hospitals and minor injury units (MIUs) in Nottingham, Bristol, Derby, Gateshead, Great Yarmouth, Newcastle upon Tyne, Norwich and Lincoln, UK. This is one of a series of case-control studies running concurrently in these study centres which employ identical methods and aim to identify modifiable risk factors for different injury mechanisms. The published protocol for the falls case–control study describes the methods in more detail.^38^

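### Study centre is not among the named adjustment terms for the unmatched hospital-control models, so control of between-centre differences is not assured

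*Protocol article*

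**What the plan says.** The Analysis section of the protocol article sets out two families of models. The matched (conditional) models adjust a priori for deprivation and distance from hospital. For the unmatched (unconditional) models the rule is "All models will a priori be adjusted for age, gender, deprivation and distance from hospital, in addition to other potential confounding variables". That sentence goes on to refer to the approach used for the matched analysis, in which causal diagrams select a minimal adjustment set. Table 1 lists the potential confounders to be measured; study centre and recruitment date are not among them.

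The Study design section names the sites: "Nottingham, Bristol, Derby, Gateshead, Great Yarmouth, Newcastle upon Tyne, Norwich and Lincoln, UK". It adds that the parallel studies run at the same time in these centres with the same methods.

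Under Recruitment of cases and controls, community controls are drawn from the case's GP practice, or the closest one if that practice declines, and are matched on age and gender. By contrast, "Hospital controls will comprise children already recruited as a case to one of the other ongoing case–control studies". No quota, matching or balancing by centre is described for them. The Abstract says that they attend the same hospitals and minor injury units as the cases, and calls them an additional control group.

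**The concern.** A community control shares three things with its case: age band, gender and, through the GP practice, place. When the matching is dropped for the hospital-control comparison, the a priori list restores age and gender but not place. Distance from hospital does not replace it, because the same distance from two different hospitals is coded alike. Deprivation captures only part of any difference between areas.

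Centre confounds these ORs if two things vary together across centres: the ratio of recruited scald cases to recruited fall and poisoning cases, and the prevalence of the safety practice or hazard. The protocol guarantees neither an equal ratio nor equal prevalence.

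What is at stake is the second set of ORs. The Discussion presents the use of both control groups as one way to limit bias. If one analysis handles place and the other may not, a disagreement between them is harder to interpret.

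**Working it through.** **The plan's own figures.** The Sample size section gives one number only, and it is for the matched analysis: "259 cases and 1036 matched controls are required to detect an OR of 0.64". The section restates this effect as 1.56 for an exposure that raises risk. Its other inputs are power of 80%, significance at 5%, an exposure correlation of 0.1 within matched sets, and a mean control:case ratio of 4.

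- 4 × 259 = 1036, and 1/0.64 = 1.5625, so these figures agree with each other.
- Dupont's matched case-control formula (four controls per case, correlation 0.1, 80% power, 5% taken as two-sided) gives 258.7 cases at a control exposure prevalence of 0.33 and 257.3 at 0.77, with no allowance for missing data. At prevalence 0.40 with 10% missing it gives 230.4/0.90 = 256.0.
- The stated number is therefore attainable. It cannot be reproduced uniquely, because the prevalence and missing-data figures behind it are not printed. It has no bearing on the covariate question. No size is given for the hospital-control analysis.

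**Size of possible centre confounding.** All inputs here are assumptions except the number of centres (eight, Study design).

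- Within every centre the true OR is 1.
- Exposure prevalence in centre j (j = 1 to 8) is p_j = 0.60 − s/2 + s(j − 1)/7, where s is the spread.
- Hospital controls are split equally across centres, so their prevalence is P0 = 0.60.
- The share of cases in centre j is proportional to r^((j − 1)/7), so the case:control ratio rises r-fold from the lowest- to the highest-prevalence centre.
- P1 = Σ (case share in centre j × p_j), and the crude OR = [P1/(1 − P1)] / [P0/(1 − P0)].

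Worked example, s = 0.20 and r = 2: P1 = 0.6147, so OR = (0.6147/0.3853)/(0.60/0.40) = 1.595/1.5 = 1.06.

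| Prevalence spread | r = 1 | r = 1.5 | r = 2 | r = 3 |
|---|---|---|---|---|
| 10 points | 1.00 | 1.02 | 1.03 | 1.05 |
| 20 points | 1.00 | 1.04 | 1.06 | 1.10 |
| 30 points | 1.00 | 1.06 | 1.10 | 1.16 |

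The reciprocals, which apply if the exposure is coded the other way round, run from 0.98 (1/1.018) to 0.86 (1/1.157). The column r = 1 shows that there is no bias when the ratios are equal, whatever the prevalence spread.

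**A simpler two-group illustration, also assumed.** Half the centres have 50% exposure and half 65%. Cases split 60:40 between the two halves and hospital controls 40:60.

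- Cases: 0.6 × 0.50 + 0.4 × 0.65 = 0.56.
- Controls: 0.4 × 0.50 + 0.6 × 0.65 = 0.59.
- Crude OR = (0.56/0.44)/(0.59/0.41) = 0.884 with no true effect.
- On the log scale this is ln 0.884 / ln 0.64 = −0.123/−0.446, about 28% of the effect that the study is sized to detect.
- It implies case:control ratios of 1.5 and 0.67 in the two halves, a 2.25-fold difference.

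Both sets of figures are before adjustment for deprivation and distance, and both assume that prevalence and ratio are perfectly aligned. They mark the upper end for the inputs chosen.

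**The case against.** A reader might infer that the models are fixed without centre. The text does not support that. The a priori list is a minimum, and further confounders are to be chosen with causal diagrams, so nothing excludes centre. Table 1 covers measures taken by parent questionnaire, where an administrative variable would not naturally appear. The article is also condensed: it points to the published falls protocol for more detail, and a fuller document may name centre. All of this stands as a limit on the point. It does not dispose of it. The article does state an a priori list for the unmatched models, and the process that it borrows was described for a design in which place is largely handled by shared practices. A diagram drawn for that design has little reason to select centre.

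A reader might also infer that the hospital-control ORs are in fact biased. There are no centre-level figures on recruitment or exposure to show it. Cases and hospital controls attend the same sites, and the studies run together with identical methods. That limits imbalance, although sharing sites does not make the ratio of scalds to other injuries the same at each of them.

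A similar argument for calendar period is weaker. The studies run concurrently, and nothing here quantifies an effect of date. Nor should one say that the omission alone makes the two sets of ORs non-comparable, since they already differ in the source of controls.

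**Conclusion.** The point holds in a limited form. Study centre is absent from both the a priori terms and the listed confounders for the unmatched models, so its control depends on the causal diagrams and is not assured. The ORs can be confounded; the documents do not show that they are. Under the assumed ranges the distortion of a null OR is modest: about 1.02 to 1.16, or 0.86 to 0.98 in the other direction, and none with equal case:control ratios. For comparison, the design effect is an OR of 0.64 (1.56 for a risk factor). Only the additional control-group analysis is concerned. The matched analysis, which carries the sample size, broadly accounts for place through the GP practice and is unaffected. This is an inexpensive improvement to a stated rule and does not call the main analysis into question.

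**What to change.** In the Analysis section, add study centre to the a priori terms of every case versus hospital-control model, either as a fixed effect or by conditioning on centre. With eight centres the fixed effect uses 8 − 1 = 7 degrees of freedom against a planned 259 cases. The cost is one sentence. The article does not say that centre is held as an analysis variable, but it should be known from where each child was recruited. Recruitment period may be added as a secondary check. If a fuller protocol or analysis plan already names centre for these models, stating so in the article is enough.
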